## Abstract

**Background:**

Ambulatory phlebectomies and foam sclerotherapy are two of the most common treatments for varicose vein tributaries. Many studies have been published on these treatments, but few comparative studies have attempted to determine their relative effectiveness.

**Methods/design:**

This is a prospective single-centre randomised clinical trial. Patients with primary truncal vein incompetence and varicose vein tributaries requiring treatment will be assigned randomly to either ambulatory phlebectomies or foam sclerotherapy. The primary outcome measure is the re-intervention rate for the varicose vein tributaries during the study period. The secondary outcomes include the degree of pain during the first two post-operative weeks and the time to return to usual activities or work. Improvements in clinical scores, quality of life scores, occlusion rates and cost-effectiveness for each intervention are other secondary outcomes. The re-intervention rate will be considered from the third month.

**Discussion:**

This study compares ambulatory phlebectomies and foam sclerotherapy in the treatment of varicose vein tributaries. The re-intervention rates, safety, patient experience and the cost-effectiveness of each intervention will be assessed. This study aims to recruit 160 patients and is expected to be completed by the end of 2019.

**Trial registration:**

ClinicalTrials.gov, NCT03416413. Registered on 31 January 2018.

**Electronic supplementary material:**

The online version of this article (10.1186/s13063-019-3398-0) contains supplementary material, which is available to authorized users.

## Background

Approximately one-third of the adult population have varicose veins [1]. Chronic venous disease causes a significant negative effect on the quality of life (QoL) of patients; however, there is a significant improvement in the QoL following treatment for varicose veins [2–4].

Over the last 15 years, minimally invasive endovenous techniques for treating varicose veins have been introduced. These techniques have been proved to be cost-effective and safe, particularly when performed under a local anaesthetic in an outpatient setting [5]. The American Venous Forum and the National Institute for Health and Care Excellence have recommended endovenous thermal ablation techniques, namely radiofrequency ablation or endovenous laser ablation, as the first-line treatments for truncal reflux since 2011 and 2013, respectively [6, 7].

However, the treatment of prominent varicosities can be undertaken concurrently or at a later date using either ambulatory phlebectomy (AP) or foam sclerotherapy (FS) [6, 7]. Carradice and colleagues compared the concomitant treatment of varicosities to delayed treatment using AP following endovenous laser ablation of truncal veins [8]. Their data demonstrated that one patient (4%) in the concomitant group needed to have a re-intervention at 6 weeks compared to 16 out of 24 in the delayed treatment group [8].

Moreover, Lane et al. conducted a prospective comparative randomised trial comparing delayed AP against simultaneous AP after radiofrequency ablation. Their results showed that 2% of patients in the simultaneous group needed another intervention compared to 36% in the delayed group (*P* < 0.001) [9]. The relative risk that patients would require further varicosity treatment was 18.36, while the odds ratio was 27.78. In recent work by Gibson et al. with 50 patients, 65% of the patients required adjunctive treatment after 3 months of treating truncal veins with cyanoacrylate [10].

De Roos et al. compared sclerotherapy and AP [11]. They found that the recurrence rate at 1 year following sclerotherapy was 25% compared to 2.1% in the phlebectomy group. The relative risk for recurrence at 1 year was 12 and the odds ratio was 15.67. After 2 years, the recurrence rate was 37.5% in the sclerotherapy group with a relative risk of 18 and odds ratio of 28.20 [10]. The study, however, considered only the lateral anterior vein and used a liquid sclerosant rather a foam sclerosant, so that these results cannot be generalised to tributaries treated after truncal vein ablation using FS.

We, therefore, propose to undertake a randomised study comparing FS with AP to treat varicose vein tributaries concurrently with endovenous truncal ablation. The study is designed as a parallel group superiority study.

### Objectives

The primary objective is to ascertain the re-intervention rate following treatment with each modality. Pain score over the first 2 weeks will be assessed as a secondary objective using a 100-mm visual analogue scale and a numerical scale from 0 to 10. As additional secondary objectives, we will assess QoL, Venous Clinical Severity Score (VCSS), degree of bruising and phlebitis, patient satisfaction, time to return to normal activities and cost-effectiveness.

## Methods/design

### Study setting

Eligible patients will be recruited from Charing Cross Hospital (Imperial College London, UK).

### Eligibility criteria

Inclusion criteria are primary truncal vein incompetence and varicose vein tributaries requiring treatment. Participants must be 18 years old or older. Exclusion criteria are current deep vein thrombosis, recurrent varicose veins, arterial disease (ankle brachial pressure index < 0.8), vein diameter <3 mm, unwillingness to participate, inability or unwillingness to complete the questionnaires or attend follow-up appointments, preference for one of the treatment options or currently enrolled in a study of varicose vein treatments.

### Interventions

All eligible patients will be comprehensively informed about the study and given a written information sheet. If they agree to take part in the study, they will be asked to sign a consent form. Following study enrolment, patients will be randomised to receive either of the two study interventions (AP or FS) to treat their varicose tributaries after having their truncal saphenous veins treated (Fig. 1). At the time of randomisation, each patient will then be allocated a unique study number to maintain confidentiality.

**Fig. 1 Fig1:**
[figure not shown]
Trial flowchart. AVVQ Aberdeen Varicose Vein Questionnaire, CIVQ-14 Chronic Venous Insufficiency Questionnaire, EQ-5D EuroQol Five-Domain Utility Index, VCSS Venous Clinical Severity Score

At the baseline, basic demographic data will be collected for each patient. Patients’ contact details will also be collected to enable the scheduling of follow-up appointments. At the pre-intervention evaluation, patients will be asked to complete the following QoL questionnaires: the EuroQol five-domain utility index (EQ-5D), the Aberdeen Varicose Vein Questionnaire (AVVQ) and the Chronic Venous Insufficiency Questionnaire (CIVIQ). Their VCSS will be also assessed.

Following treatment of the truncal saphenous vein, adjuvant AP or FS will be carried out. AP is performed under either a local or a general anaesthetic, usually with a vein hook to enable venous extraction through micro-incisions [12, 13]. FS is guided by an ultrasound scan according to Tessari’s method to create a stable and compact sclerosant foam [14, 15]. Sclerosants used include sodium tetradecyl sulphate and polidocanol. This study will utilise sodium tetradecyl sulphate.

Post-intervention, all patients will be given a diary in which they will be asked to record their post-procedural pain every day for 10 days using a validated 100-mm visual analogue scale and asked to record when they are able to return to their normal daily activities and to work. Verbal and written instruction will be given on how the diary should be completed. In both groups, patients will be asked to wear compression stockings (class II 18–24 mmHg) for 1 week post-treatment and they will be advised to be active as much as possible. Each patient’s general practitioner will be sent a letter informing them of their patient’s participation in the study.

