### Follow-up treatment periods

For this research, patients will be seen in the research clinic for follow-ups at 2 weeks, 3 months, 6 months and 12 months (Fig. 2). At the 2-week follow-up, the patient’s diary will be collected, but no decision regarding re-treatment will be taken. At all follow-ups, they will undergo a clinical assessment and their VCSS will be recorded. Additionally, patients will be asked to fill out the EQ-5D, AVVQ and CIVIQ-14 questionnaires. All patients will be asked how satisfied they were with their treatment using a satisfaction questionnaire (ranging from 0 = very bad to 10 = excellent). At the 3-, 6- and 12-month follow-ups, a duplex ultrasonographic scan will be carried out to determine if there is occlusion of the treated vein.

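### The pain outcome is defined over two weeks and on two scales, but the diary described records 10 days on one scale; return dates have no described capture after about two weeks

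*Protocol article*

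**What the plan says.** **Window.** The Methods/design part of the abstract names among the secondary outcomes "the degree of pain during the first two post-operative weeks". The Objectives section says "Pain score over the first 2 weeks will be assessed as a secondary objective", and the Secondary outcomes section lists pain over the same period. The Interventions section has patients "record their post-procedural pain every day for 10 days using a validated 100-mm visual analogue scale".

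**Scale.** The Objectives section says that pain will be measured "using a 100-mm visual analogue scale and a numerical scale from 0 to 10". The diary in the Interventions section uses the visual analogue scale alone.

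**Return to work and activities.** In the same diary, patients are "asked to record when they are able to return to their normal daily activities and to work". The section on follow-up says "At the 2-week follow-up, the patient’s diary will be collected". The Secondary outcomes section sets no upper limit on these times.

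**Analysis.** The Statistical analysis section gives *t*-tests or Mann–Whitney tests for data in general, and names both listwise deletion and multiple imputation for missing values. It describes survival methods with censoring for re-intervention. It names no method for the return times.

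**The concern.** Three sections promise a two-week pain outcome, and the section that says how pain is collected stops at day 10. This is a contradiction within the article, not a detail left to an analysis plan. Measurements that were never requested cannot be supplied by a later plan. Multiple imputation does not help either, because on the described collection no patient has a value on days 11 to 14 from which to build an imputation model.

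The two scales add a second ambiguity. With two possible windows and two named instruments, and no statement of which is analysed, the choice could be made after the data are seen.

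Return to work and activities shares the diary. A patient not yet back when the diary is handed in has no recorded date, although it is known that the time exceeds about two weeks. The general missing-data rules do not use that knowledge. Time to return to work also enters the cost-effectiveness analysis, so its handling matters beyond the clinical comparison.

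**Working it through.** **Design calculation.** The article gives no figure for pain or return times. Its only design calculation is for the primary outcome: 58 per group for 5% against 25% at 80% power and a 5% level. The two-proportion formula with continuity correction, two-sided, gives 59, so the stated figure reproduces closely. Neither pain nor return times enter that calculation.

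**Pain window.**
- Outcome window: 2 weeks = 14 days (abstract, Objectives, Secondary outcomes).
- Diary length: 10 days (Interventions).
- Covered: 10 / 14 = 71%.
- Not covered: 14 − 10 = 4 days; 4 / 14 = 29%.

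This assumes that the diary and the two-week window start on the same day.

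**Could another measurement fill the gap?** For the 2-week visit and for all follow-ups, the text lists diary collection, clinical assessment, clinical severity score, the three quality-of-life questionnaires and a satisfaction score. Neither a visual analogue nor a numerical pain rating is listed.

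**Pain scale, side by side.**

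| Section | 100-mm visual analogue scale | 0 to 10 numerical scale |
|---|---|---|
| Objectives | named | named |
| Interventions (diary) | collected daily | not mentioned |
| Secondary outcomes | no scale given | no scale given |
| Follow-up treatment periods | not mentioned | not mentioned |

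**Return times.** The 10-day limit is attached to the pain recording. The request to note return to activities and work is a separate clause with no day limit. The patient keeps the diary until the 2-week visit, so the described capture runs to about day 14. Visits follow at 3, 6 and 12 months, but the text does not say that outstanding return dates are requested there. The article gives no distribution of return times, so the proportion not yet back at about day 14 cannot be calculated.

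**The case against.** **The pain comparison survives in a usable form.** Both arms keep the same 10-day diary, so a like-for-like comparison over days 1 to 10 remains possible. This stands. What is lost is the outcome as defined, and no bias between the arms follows from the shorter window alone.

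**The schedule figure is not shown.** Fig. 2 could place the numerical scale, a pain rating at two weeks or a later question on return dates. This also stands, and it limits the claim to collection not being described in the text. It does not remove the conflict between a 10-day diary and a two-week outcome, which is in the text itself.

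**Pain is one of several secondary outcomes.** No hierarchy is declared. The abstract and objectives mention pain first, but the outcome list places it fourth. The point should not be presented as touching a key endpoint.

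**Return times: a stronger reading is tempting.** A reader might infer that return times beyond the diary are lost, that slow recoverers are deleted and the remainder analysed as complete, and that the comparison is biased towards no difference. The document does not support this. The 10-day limit does not govern these items. Multiple imputation is named alongside listwise deletion. No method is assigned to return times, and later visits exist at which dates could be asked. An article may also leave such handling to the full protocol or analysis plan. What remains is narrower: the only described capture ends at about two weeks, the outcome has no stated upper limit, and censoring is stated for re-intervention only.

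**Conclusion.** The pain point holds as a contradiction. As written, 4 of the 14 days in the outcome window (29%) have no collection described for any patient, and one of the two named scales has no described collection at all. The outcome stated in the abstract, the objectives and the outcome list cannot be computed from the diary in the Interventions section. This rests on the text alone, with the schedule figure not available.

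The point on return to work and activities holds only as a secondary one: what happens to patients not yet back when the diary is collected is not settled by the text. Neither the direction nor the size of any bias can be asserted.

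Both matters concern secondary outcomes, and both should be corrected. The re-intervention outcome and its sample size are unaffected.

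**What to change.** 1. **Make the pain diary and outcome the same length.** Either extend the pain diary to 14 days, or redefine the outcome as days 1 to 10 in the abstract, Objectives and Secondary outcomes. The first option costs four more diary entries per patient and no extra visit, since the diary is already collected at two weeks. The second costs a wording change. If 10-day diaries have already been completed, the second option keeps one window for all patients.

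2. **Settle the scale.** Name the 100-mm visual analogue scale as the one analysed. Delete the numerical scale from the Objectives, or state when it is collected and what it is used for.

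3. **Close the gap in return times.** At the existing 3-month visit, ask patients who were not yet back at diary collection for the dates on which they returned to work and to normal activities. Treat those still not back as censored, rather than deleting or imputing their times. This costs one question at a visit already planned and one sentence in the analysis section. The survival methods needed are already planned for re-intervention.

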### Primary outcome

The primary outcome of this study is the re-intervention rate at 12 months.

### Secondary outcomes

The secondary outcomes include:QoL scores at baseline, 2 weeks, 3 months, 6 months and 12 months using the EQ-5D, AVVQ and CIVIQ-14The clinical change in the VCSS from the baseline at 2 weeks, 3 months, 6 months and 12 monthsThe degree of bruising and phlebitis at 2 weeks (based on a clinical examination)The pain score over the first 2 weeksVisual (cosmetic) appearance at baseline, 2 weeks, 3 months, 6 months and 12 monthsThe time taken to return to work and normal activitiesPatient satisfaction at 2 weeks, 3 months, 6 months and 12 monthsCost-effectiveness

### Sample size and study duration

From the published literature, we anticipate a re-intervention rate of 5% in the AP group and 25% in the FS group. Utilising Pearson’s chi-squared test, with a power of 80% at the 5% significance level, 58 patients per group (for a total of 116) would be required to detect an absolute difference of at least 20% in the re-intervention rates. ﻿Assuming﻿ a drop-out rate from follow-up of about 30%, we estimate that 160 patients would be required in total. It is assumed that at least three eligible patients will be enrolled per week, giving a total of 156 patients who could potentially be randomised over the year. With the 12 months of follow-up, this study will run for 24 months.

### Recruitment

All patients referred for treatment of symptomatic varicose veins will be included if they also have primary truncal vein incompetence and visible symptomatic varicosities needing treatment. Potential patients will be identified at outpatient clinic appointments and given a patient information sheet.

### Follow-up treatment periods

For this research, patients will be seen in the research clinic for follow-ups at 2 weeks, 3 months, 6 months and 12 months (Fig. 2). At the 2-week follow-up, the patient’s diary will be collected, but no decision regarding re-treatment will be taken. At all follow-ups, they will undergo a clinical assessment and their VCSS will be recorded. Additionally, patients will be asked to fill out the EQ-5D, AVVQ and CIVIQ-14 questionnaires. All patients will be asked how satisfied they were with their treatment using a satisfaction questionnaire (ranging from 0 = very bad to 10 = excellent). At the 3-, 6- and 12-month follow-ups, a duplex ultrasonographic scan will be carried out to determine if there is occlusion of the treated vein.

**Fig. 2 Fig2:**
[figure not shown]
Schedule of enrolment, interventions and assessments

All participants will be sent reminders by post or contacted over the telephone to attend the follow-up visits. If they fail to attend a scheduled visit, the QoL questionnaires will be sent by post to be completed.

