### Re-intervention

No decision regarding re-intervention will be made before the 3-month follow-up. From this point, any recurrence of tributaries will be assessed from the patent’s history and a physical examination at the 3-, 6- and 12-month follow-ups. Re-intervention is indicated by the symptomatic recurrence of varicosities in the areas previously treated that are deemed to necessitate treatment by both the clinician and the patient. The method used for re-intervention will be chosen by the clinician who is caring for the patient.

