### Statistical analysis

Data collected from each patient will be entered into and analysed using the statistical software package SPSS version 24 (IBM, Armonk, New York, USA), STATA 15SE (STATACorp, College Station, Texas, USA) and Wizard Pro v1.9.29 (Evan Miller, Chicago, USA).

All analyses will be carried out on an intention-to-treat basis. To determine the normality of the data, both a visual test and a Shapiro–Wilk test will be used. If the data are normally distributed, the mean and standard deviation will be reported, otherwise the median and interquartile range. Categorial variables will be presented as frequencies and percentages. If the data are normally distributed, *t*-tests will be used or the Mann–Whitney *U* test if not. Assessments of the changes in scores from the baseline to each follow-up visit will be investigated using a repeated measures ANOVA. The primary outcome measure is a comparison of the re-intervention rates between groups at 12 months. This will be assessed with a Mann–Whitney *U* test.

The data will be assessed for missing values. The complete data set will be analysed using the listwise deletion methodology. The multiple imputation methodology will be used for missing data points.

Freedom from re-intervention curves will be analysed utilising survival analysis and Kaplan–Meier estimation methods with re-intervention classified as the failure event. Missing values for re-intervention due to loss to follow-up will be censored in the survival analysis.

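### The stated missed-visit procedure collects quality-of-life questionnaires but not re-intervention, the primary outcome, although post and telephone contact already in use could recover some of it

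*Protocol article*

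**What the plan says.** All of this is in the protocol article.

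- **Primary outcome:** "The primary outcome of this study is the re-intervention rate at 12 months".
- **Re-intervention:** recurrence is assessed from the history and "a physical examination at the 3-, 6- and 12-month follow-ups". Re-intervention is indicated for symptomatic recurrence in areas already treated, when clinician and patient both judge that treatment is needed.
- **Follow-up treatment periods (text after Fig. 2):** "All participants will be sent reminders by post or contacted over the telephone to attend the follow-up visits". For a missed visit, the stated procedure is: "If they fail to attend a scheduled visit, the QoL questionnaires will be sent by post to be completed". The questionnaires named for follow-up are EQ-5D, AVVQ and CIVIQ-14, and the Secondary outcomes section lists all three.
- **Sample size and study duration:** drop-out from follow-up is put at about 30%, and 116 evaluable patients are raised to 160 recruited.
- **Statistical analysis:** "Missing values for re-intervention due to loss to follow-up will be censored in the survival analysis". Listwise deletion and multiple imputation are named for missing data more generally, and all analyses are to be by intention to treat.

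**The concern.** The article gives a rule for the missed visit, and that rule rescues secondary outcomes while naming nothing for the primary one. The contact it relies on, a letter and often a call, could carry a question about further treatment at almost no cost. Followed as written, the plan lets a patient who stops attending but would answer a letter return three quality-of-life forms and still have a missing primary outcome.

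Two things are at stake. One is information, since each recovered status adds to the evaluable sample. The other is credibility. If attendance depends on whether varicosities have come back, and does so differently by arm, then neither censoring nor imputation under the usual assumptions removes the bias. Patients know their allocation, and the outcome depends partly on their wish for treatment, so such a link is plausible. The documents do not show it.

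**Working it through.** **Inputs.** From Sample size and study duration: planning rates 5% for phlebectomy and 25% for foam; chi-squared test with 80% power and a 5% level; 58 evaluable per group; drop-out about 30%; 160 in total. Randomisation is equal, so 80 per arm. Sidedness is not stated, and I take two-sided.

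**1. The plan's own figure.** With mean rate 0.15 and difference 0.20:

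n = [1.96·√(2·0.15·0.85) + 0.8416·√(0.05·0.95 + 0.25·0.75)]² / 0.20² = 48.8 per group, so 49 without continuity correction.

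With correction: n/4 · [1 + √(1 + 4/(n·0.20))]² = 58.4. This is the variant that matches the stated 58.

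**2. Size of the gap.** 0.30 × 160 = 48 patients, 24 per arm, leaving 56 per arm (112 in total) with the outcome known. At the planning rates the observed events are 56 × 0.05 = 2.8 after phlebectomy (AP) and 56 × 0.25 = 14 after foam (FS).

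**3. Extreme-case bounds on FS minus AP, all 80 per arm.** Let m be the share missing in each arm.

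- Lower (all missing AP patients have events, no missing FS patients do): 0.25(1−m) − [0.05(1−m) + m] = 0.20 − 1.2m
- Upper (the reverse): [0.25(1−m) + m] − 0.05(1−m) = 0.20 + 0.8m

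| Missing share | Evaluable of 160 | Lower | Upper |
|---|---|---|---|
| 30% (plan) | 112 | −16 points | +44 points |
| 15% (assumes half recovered) | 136 | +2 points | +32 points |
| 10% (assumed) | 144 | +8 points | +28 points |

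These bounds carry no sampling error. At the lower 10% bound the rates are 0.225 for FS and 0.045 + 0.10 = 0.145 for AP. The standard error is √(0.225·0.775/80 + 0.145·0.855/80) = 0.061, so a 95% interval is 8 ± 12, about −4 to +20 points.

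**4. Less extreme departures, 30% missing.** True difference = 0.7 × 0.20 + 0.3 × (rate in lost FS − rate in lost AP). All rates in lost patients are assumed.

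| Lost AP | Lost FS | True difference |
|---|---|---|
| 5% | 25% | 20 points (no bias) |
| 25% | 25% | 14 points |
| 50% | 25% | 6.5 points |
| 5% | 50% | 27.5 points |

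Bias can run in either direction, and its size depends on rates the plan gives no way to learn.

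**5. Power at 5% against 25%.**

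| Share of the lost recovered (assumed) | Per arm | Uncorrected | Continuity-corrected |
|---|---|---|---|
| none | 56 | 85.2% | 77.9% |
| half | 68 | 91.3% | 86.7% |
| 80% | about 75 | 93.8% | 90.3% |
| all | 80 | 95.0% | 92.2% |

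**The case against.** **The article is condensed.** It does not say that re-intervention is sought by no other route, the assessment schedule in Fig. 2 is not shown, and a fuller protocol may hold a telephone script or a record check. This stands as a limit: that nothing but questionnaires is collected is a reading of the text. But the article does state its missed-visit procedure, and names only quality-of-life forms in it.

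**A reader might infer that the primary outcome is lost in exactly the 30% expected to drop out.** The text does not support that. Drop-out is given as about 30%, and missing one visit is not dropping out: someone absent at 3 or 6 months may report re-treatment at 12. True drop-outs may also ignore a letter or call.

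**A reader might infer that a question or the hospital record would fully supply the outcome.** It would not. A postal answer is self-report by an unblinded patient, without examination. Need is judged at study visits and treatment may happen elsewhere, so a clean hospital record does not make a non-attender event-free. Treating it so would replace missing data with false negatives.

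**A reader might infer that censoring here is informative and the result biased.** No section links attendance to recurrence, and bias in the difference also depends on how such a link differs by arm. Censoring is confined to the survival analysis. Multiple imputation is planned as well, and the posted AVVQ and CIVIQ scores could inform it. That softens the point, but imputing an outcome is weaker than asking for it.

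**The sample size already allows for drop-out.** With the uncorrected test, 56 per arm still gives 85.2% power, so the case does not rest on a power shortfall. The gap between 112 and the required 116 is a separate matter of sample-size inflation.

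**Conclusion.** The point holds as a cheap improvement. It is neither a contradiction in the plan nor evidence of bias. The stated fallback leaves some primary-outcome data uncollected that contact already in use could recover.

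At 30% missing in each arm and the planning rates, the missing share exceeds the expected 20-point effect, and the bounds of −16 to +44 points include zero. They are the most extreme cases possible, not likely values. Narrower bounds at 15% or 10% missing rest on assumed recovery. It would be wrong to conclude that 10% missing settles the question: with sampling error, the worst case still reaches about −4 points.

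**What to change.** Add to Follow-up treatment periods, beside the posted questionnaires:

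1. After any missed visit, the postal pack and the reminder call also ask whether varicosities in the previously treated areas have been treated again, with date and place. Treatment offered but not done is recorded separately.
2. At 12 months, the centre's procedure records are used only to confirm or add performed re-interventions. Absence of a record does not count as event-free.

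Add to Statistical analysis:

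3. Performed re-interventions found by these routes count in the primary analysis. Patients are censored at the last date on which their status is known.
4. A sensitivity analysis is limited to clinic-assessed events.

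**Cost:** one or two questions on an existing mailing and call, one record check per patient, and one extra analysis. No treatment or clinical rule changes. **Downside:** some events will be unblinded self-report without examination, and untreated recurrence in non-attenders stays unobserved.
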